### Participant timeline

The overview of the study schedule, including enrolment, intervention and assessments, is presented in table 2.

**Table 2 T2:** Study schedule

	Enrolment	Allocation and intervention	Intervention	Post-intervention	
Time point	Studies which are sent out for peer review	After first peer reviewer accepts invitation	Whenever an additional peer reviewer accepts invitation	First decision by journal	Published manuscripts
Eligibility screen	X				
Allocation		X			
Intervention:					
C-short + usual care		X	X		
Usual care		X	X		
Assessment of trial characteristics:					
Funding source					X
Study centres (single centre or multicentre)					X
Sample size					X
Study design (eg, parallel arm, crossover)					X
Hypothesis (eg, superiority, non-inferiority)					X
Medical field					X
Intervention tested					X
Number of trial arms					X
Number of peer reviewers					X
Journal which published the manuscript					X
Number of journals requesting CONSORT adherence (submission of checklist mandatory)					X
Assessment of outcomes:					
Time from assigning an academic editor until the first decision				X	
Proportion of manuscripts directly rejected after the first round of peer review				X	
Proportion of manuscripts that will be published in the journal under study					X
Adherence to CONSORT items and sub-items					X

CONSORT, CONsolidated Standards of Reporting Trials.

### Sample size

For the sample size calculation, we hypothesised in a first scenario (table 3) that the intervention C-short will result in a 25% relative increase in adequate reporting compared with the control (meaning that 70% of items will be adequately reported in the intervention group and 56% in the control group). This is based on a proportion of adequate reporting of 0.56 for the 10 most important and poorly reported items found in the control group of a previous study (meaning that a mean of 56% of the 10 most important and poorly reported items were reported).^30^ The SD in the same study was 0.23. However, we calculated our sample size to account for a slightly larger variability in our data (SD=0.25). To demonstrate a significant difference with a power of 90% and a type 1 error at 5%, a total of 136 published articles will be required in this scenario (68 per treatment arm; based on a two sided t-test).

**Table 3 T3:** Assumptions for sample size calculations in two different scenarios

Item	CONSORT item	Scenario 1. adequate reporting as published in WebCONSORT^30^	Scenario 2. adapted from scenario 1
1	Outcomes (6a)	77% (79 of 103)	77% (79 of 103)
2	Sample size (7a)	83% (85 of 103)	83% (85 of 103)
3	Sequence generation (8a)	76% (78 of 103)	76% (78 of 103)
4	Allocation concealment (9)	55% (57 of 103)	55% (57 of 103)
5	Blinding (11a)	35% (36 of 103)	35% (36 of 103)
6	Outcomes and estimation (17a	44% (45 of 103)	44% (45 of 103)
7	Harms (19)	71% (73 of 103)	71% (73 of 103)
8	Registration (23)	69% (71 of 103)	90%
9	Protocol (24)	19% (20 of 103)	90%
10	Funding (25)	34% (35 of 103)	90%
**Overall**		**56%**	**71%**

CONSORT, CONsolidated Standards for Reporting Trials

Two authors of this protocol, working for *PLOS ONE* (IP and AC), one of the participating journals, pointed out that 3 out of the 10 assessed items (ie, item ‘Registration’, ‘Protocol’ and ‘Funding’) should always be implemented in submissions to their journal given their policy requirements for clinical trials. Assuming that this journal will recruit a high proportion of manuscripts, and that also other journals might update their templates, we increased the sample size in a second scenario, in which all these three items would have an overall adherence of 90% in the control arm (table 3). This would entail an overall baseline adherence with the 10 C-short items of 71%. Based on a two sided t-test, a sample size of 166 (83 per treatment arm) will have a power of 80% to find a 15% relative increase (71% adherence in control group; 82% adherence in intervention group; SD=0.25; a type 1 error at 5%).

Since the final sample size will be based on the number of articles published, rather than on the number of manuscripts randomised, eligible manuscripts will be randomised until 83 articles are published in each arm (resulting in no less than 166 articles), to avoid loss of power due to potential imbalance between arms. Recruitment will be stopped as soon as both arms reach the sample size of 83. After recruitment has stopped we will wait 3 months so that manuscripts, which are still in production, can be published. Manuscripts which are published after the 3-month period will be excluded.

### Randomisation and blinding

Manuscripts meeting the eligibility criteria and sent out for external peer review by the journals will be randomised into one of the two groups (allocation 1:1). The randomisation list will be created by the Study-Randomizer system^34^ using random block sizes between 2 and 8 and stratified by journal. As soon as the first peer reviewer accepts the invitation, the manuscript will be included and randomised to one of the two study arms. One of the investigators (BS) will log onto the Study-Randomizer system^34^ and enter the study identification number (ID; provided by the journal), the study title and the journal the study was submitted to. Subsequently, all additional peer reviewers accepting the invitation to review the same manuscript will receive the same group assignment as the first peer reviewer.

Authors will be blinded to the intervention. Editors will not be actively informed about the randomisation (possible exception listed under ‘Interventions’). To avoid potential bias, peer reviewers and manuscript authors will not be informed of the study hypothesis, design and intervention.

Outcomes will be assessed in duplicate (see ‘Assessment of outcomes’). At least one outcome assessor will be blinded. Due to restricted resources the investigator conducting the randomisation (BS) might be involved in the data extraction from published manuscripts.

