#### Intervention group: C-short plus usual practice

After accepting to review a manuscript, peer reviewers will receive the automated, journal specific standard email with general information (identical to control group). In addition, peer reviewers will receive an additional email from the editorial office that includes a short version of the CONSORT checklist (C-short) together with a brief explanation of the items either as a table within the email or as an attachment based on the preferences and possibilities of the journal (table 1, online supplementary appendix 1). Peer reviewers will be asked to check whether the items in the C-short checklist are addressed in the manuscript and to request authors to include these items if they are not adequately reported. This second email (see online supplementary appendix 1), containing the C-short checklist together with a brief explanation, is not generated automatically within the existing journal editorial systems (eg, ScholarOne or Editorial Manager); it will be sent manually by a researcher (BS) from the journal’s editorial system or by a member of the journal’s staff. In both cases the email will appear to have come from the editorial office (not the researcher).

10.1136/bmjopen-2019-035114.supp1Supplementary data

**Table 1 T1:** The 10 most important and poorly reported consort items as defined by a group of experts on the CONSORT statement.^30^for better understanding key features were summarised within a short explanation (extracted from the CONSORT explanation and elaboration paper^11^ as well as from the COBWEB tool)^33^

Item	Section	CONSORT item	Short explanation
1	Outcomes (6a)	Completely defined pre-specified primary outcome measure, including how and when it was assessed	Is it clear (i) what the primary outcome is (usually the one used in the sample size calculation), (ii) how it was measured (if relevant; eg, which score used), (iii) at what time point and (iv) what the analysis metric was (eg, change from baseline, final value)?
2	Sample size (7a)	How sample size was determined	Is there a clear description of how the sample size was determined, including (i) the estimated outcomes in each group, (ii) the α (type I) error level, (iii) the statistical power (or the β (type II) error level) and (iv) for continuous outcomes, the SD of the measurements?

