#### Additional outcomes

Exploratory analysis of available peer reviewer comments (ie, any references to CONSORT).

For journals where peer reviewers’ comments are subsequently published alongside the published article, we will examine the peer reviewers’ comments for any reference to CONSORT and trial reporting. We will contact those journals which do not make peer reviewers’ comments publicly available, to see if reviews could be provided for such analyses under the condition that only anonymised data will be published.

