#### Assessment of outcomes

The outcomes will be assessed independently by two (blinded or at least partially blinded; see ‘blinding’) outcome assessors with expertise in the design and reporting of clinical trials. Any disagreement will be resolved by consensus or if necessary by consulting a third assessor. To ensure consistency between reviewers, we will first pilot the data extraction form; any disparities in the interpretation will be discussed and the data extraction form will be modified accordingly.

Adequate reporting of items will be assessed in duplicate from published full-text publications following the same instructions as provided by the CONSORT C-short checklist.^11^ The following checklist items have, due to their complexity, sub-items which will be extracted separately. The sub-items are highlighted in the short explanation of the intervention (see table 1 and online supplementary appendix 1):

Outcomes (item 6a): (i) define primary outcome, (ii) how it was measured, (iii) at what time point and (iv) the analysis metric (eg, change from baseline, final value).Sample size (item 7a): (i) the estimated outcomes in each group, (ii) the α (type I) error level, (iii) the statistical power (or the β (type II) error level), (iv) for continuous outcomes, the SD of the measurements.Blinding (item 11a): Is the blinding status clear for the following persons: (i) healthcare provider, (ii) patients and (iii) outcome assessors.Funding (item 25): (i) the funding source, and (ii) the role of funder in the design, conduct, analysis and reporting.

All items will be judged as either ‘yes’ meaning adequately reported, ‘no’ meaning not adequately reported or not reported at all, or ‘NA’ meaning that this sub-item is not applicable for this RCT. Items with different sub-items will only be judged as adequately reported if all relevant sub-items were adequately reported.

The outcomes ‘time from assigning an editor to the first decision’, ‘proportion of manuscripts rejected after the first round of peer-review’ and ‘proportion of manuscripts that will be published in the journal under study’ will be extracted directly from the journal’s editorial system or provided by the journal.

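### The investigator who randomises may be one of the two outcome assessors, and disagreements go first to consensus, so knowledge of allocation can influence the disputed items of the primary outcome

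*Protocol article*

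**What the plan says.** Four rules in the protocol article bear on this point.

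- **Who may assess.** Randomisation and blinding states: "Due to restricted resources the investigator conducting the randomisation" "might be involved in the data extraction from published manuscripts". The minimum is given just before: "At least one outcome assessor will be blinded". Assessment of outcomes agrees with this: "The outcomes will be assessed independently by two (blinded or at least partially blinded". The Abstract repeats the minimum of one blinded extractor.
- **What that investigator knows.** The same person screens submissions and enters each manuscript's identifier, title and journal into the randomisation system. On the intervention email, the protocol says "it will be sent manually by a researcher" working in the journal's editorial system, or alternatively by journal staff.
- **What is scored.** Each item is rated yes or no, the second being defined as "no’ meaning not adequately reported or not reported at all". Items 6a, 7a, 11a and 25 have listed sub-items, and such an item counts only if every relevant sub-item is adequate.
- **How disputes end.** "Any disagreement will be resolved by consensus or if necessary by consulting a third assessor". The third assessor is not said to be blinded.

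**The concern.** Duplicate scoring with one blinded assessor works well where the two independent ratings agree. It is weakest where they differ, and those are likely to be the borderline items. Under the stated rules, someone who knows the arm takes part in the first step of settling them. That person entered the manuscript's title at randomisation, so may recognise the published article.

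The primary outcome is the difference between arms in the mean proportion of the ten items adequately reported. Any tendency to resolve borderline items more favourably in one arm goes straight into the treatment contrast. Data management and confidentiality plans no auditing or monitoring and gives duplicate extraction as a reason, so the plan relies on the very safeguard that is weakened here.

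**Working it through.** **1. The plan's own sample size.** Inputs from Sample size, scenario 2: 0.71 versus 0.82, so δ = 0.11; SD 0.25; two-sided α 0.05; power 80%.

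n per arm = 2(z₀.₉₇₅ + z₀.₈₀)² × SD² / δ² = 2 × (1.960 + 0.842)² × 0.0625 / 0.0121 ≈ 81.1, so 82 by the normal approximation. The t-test version gives 82.05, rounded up to 83, with power 80.5% at 83 per arm. The stated 83 reproduces, and nothing in this point changes it.

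**2. Where knowledge of allocation can enter.** Suppose one assessor is blinded and the other is not.

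- Both rate yes, or both rate no: the final score equals the blinded rating, so the unblinded assessor changes nothing.
- They differ: consensus is tried first. The final score is then either the blinded rating or a change to which the blinded assessor has agreed.
- No consensus: a third assessor is consulted, blinding not stated.

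The open route is therefore the disputed items. Four of the ten items are all-or-nothing over listed sub-items: 4 (6a) + 4 (7a) + 3 (11a) + 2 (25) = 13 sub-items. In these items one disputed sub-item can flip the whole item if the others are adequate.

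**3. What a shift would do (illustration).** If discordance is similar in both arms, the net shift is

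b = (share of items disputed) × (share of articles with the investigator in the pair) × (difference between arms in the chance of a yes at resolution).

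The documents give none of these three. With the investigator in every pair, assumed values give 0.10 × 1 × 0.10 = 0.01; 0.15 × 1 × 0.20 = 0.03; 0.20 × 1 × 0.20 = 0.04. With the investigator in half the pairs, the middle case falls to 0.15 × 0.5 × 0.20 = 0.015.

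SE = 0.25 × √(2/83) = 0.0388. With no true effect, the probability that the two-sided 5% test rejects is 1 − Φ(1.96 − b/SE) + Φ(−1.96 − b/SE). For b = 0.03, b/SE = 0.773, and the result is 0.1176 + 0.0031 = 0.121.

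| Assumed net shift b | Items per article | Share of planned 0.11 | Type I error |
|---|---|---|---|
| 0.01 | 0.1 | 9% | 5.8% |
| 0.02 | 0.2 | 18% | 8.1% |
| 0.03 | 0.3 | 27% | 12.1% |
| 0.04 | 0.4 | 36% | about 18% |
| 0.05 | 0.5 | 45% | 25.2% |

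The error rates follow from the shifts. The shifts themselves are assumptions.

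**4. Workload of adjudication.** 166 articles × 10 items = 1,660 final item scores. If 10% to 20% are disputed and the investigator is always in the pair, 166 to 332 items would need adjudication.

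**The case against.** The arrangement is disclosed, conditional and explained by limited resources. The protocol says only that the investigator might take part, and journal staff may send the email instead. There are real safeguards: independent duplicate scoring, assessors with expertise in trial reporting, a piloted form and written criteria for each item. Some items, such as the registry and registration number, are close to factual. An article also condenses the full protocol, so the storage of ratings or a sensitivity analysis could be described elsewhere.

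Most of this stands, and it limits how likely and how large a bias would be. It does not remove the point, which rests on two rules the article states: the one-blinded minimum and consensus first. Nothing stated makes the blinded view prevail.

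A reader might go further in three ways that the documents do not support.

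- *That one blinded assessor gives no protection when the final score is set.* A consensus needs that assessor's agreement, and otherwise the dispute goes to a third person.
- *That a bias could never be detected afterwards.* Extraction is in duplicate from published articles. If the independent ratings are kept, they can be compared by arm, and articles can be rescored.
- *That reviewer reports would unblind the scoring.* Additional outcomes says "we will examine the peer reviewers’ comments for any reference to CONSORT and trial reporting". It does not say that the outcome assessors read these reports, or when. All participating journals endorse CONSORT, so a mention of it need not reveal the arm.

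**Conclusion.** The point holds in limited form. If the randomising investigator is used as an assessor, the stated rules let knowledge of allocation influence the disputed items of the primary outcome, although never by that assessor's decision alone. Neither the size nor the direction of any bias can be derived from the documents. The table should not be read as an estimate of bias; it shows that a shift of a few tenths of an item per article would be enough to matter. It assumes SD 0.25, 83 articles per arm and no true effect, and the upper rows need both frequent involvement of the investigator and a net tilt in one direction. The rules do not contradict each other. This is an openly stated resource trade-off that can be improved cheaply.

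**What to change.** For articles where the unblinded investigator is one of the pair:

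1. Take that investigator out of the resolution step. Either let the blinded assessor's rating stand, or send the disagreement to the third assessor already in the plan, and state that this person must be blinded to arm.
2. Keep both independent ratings as entered, before any discussion.
3. Pre-specify a sensitivity analysis of the primary outcome on the blinded assessor's pre-consensus ratings alone.

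The investigator may still extract data, so the resource limit is respected, and the sample size is unchanged. Blinded adjudication would send more items to the third assessor, up to the 166 to 332 derived above if the investigator is always in the pair, which is a real burden for a small team. Letting the blinded rating stand adds no adjudication, but gives up the correction of plain extraction errors through discussion.

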### Data analysis

All quantitative variables will be described using means and SD, or medians and interquartile ranges in case severe departures from a normal distribution are identified. Data distributions will be inspected visually (ie, by histograms) instead of performing formal statistical tests for normality. Categorical variables will be described using frequencies and percentages. For the primary and secondary outcomes, we will estimate the mean difference between the two groups and report them with respective 95% CI. No interim analysis will be conducted.

#### Populations of analysis

The main population for analysis will be all manuscripts randomised and accepted for publication in the participating journals. In contrast to RCTs conducted with patients, where losses to follow-up need to be carefully considered (eg, multiple imputation of missing data), we are only interested in the reporting adherence of RCTs that are published. As such, we will exclude randomised manuscripts that were not published from the main analysis. All outcomes will be calculated based on the main population. The secondary outcome ‘Time to the first decision’ will additionally be calculated considering all randomised manuscripts (including the ones which were not published). For all analyses a p-value of 0.05 (5% significance level) will be used to indicate statistical significance. Exact p-values will be presented up to three decimal places. We anticipate there will be no missing data in this study, neither at the individual C-short items, nor at the manuscript level. This is due to the study design, which will include only the randomised manuscripts that are accepted for publication. We will analyse if the rate of manuscripts rejected after the first round of peer review and if the proportion of manuscripts that will be published differentiate among the two study arms (both secondary results).

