#### Secondary outcomes

Secondary outcomes will include the following:

Mean proportion of adequately reported C-short items in published articles considering each item separately.Difference in mean proportion of adequately reported C-short items in published articles considering each sub-item (see ‘Assessment of outcomes’) as a separate item.Time from assigning an editor to the first decision (as communicated to the author after the first round of peer review).Proportion of manuscripts rejected after the first round of peer review.Proportion of manuscripts that will be published in the journal under study.

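### The primary comparison is conditional on publication, which the intervention may change; the no-missing-data reasoning does not remove the possible selection bias

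*Protocol article*

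**What the plan says.** Under Randomisation and blinding, a manuscript enters the trial and is allocated when the first peer reviewer accepts the invitation, so every editorial decision comes after randomisation.

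Under Populations of analysis:

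- The analysis set is defined by what happens later: "The main population for analysis will be all manuscripts randomised and accepted for publication in the participating journals". The rest are dropped: "we will exclude randomised manuscripts that were not published from the main analysis". The reason given is that, unlike in patient trials where losses need careful thought, only the reporting of published trials is of interest.
- On missing data: "We anticipate there will be no missing data in this study, neither at the individual C-short items, nor at the manuscript level". The justification follows: "This is due to the study design, which will include only the randomised manuscripts that are accepted for publication".
- On the population for the other outcomes: "All outcomes will be calculated based on the main population". Only time to first decision is extended to all randomised manuscripts.

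The Secondary outcomes list includes "Proportion of manuscripts rejected after the first round of peer review" and "Proportion of manuscripts that will be published in the journal under study", and Populations of analysis says both will be compared between arms. The Sample size section adds a further exclusion after randomisation, for articles published more than 3 months after recruitment stops.

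**The concern.** Reviewers in one arm are asked to look for ten reporting items and to request any that are missing. That can improve the published article, which is the intended route. It can also change which manuscripts are published: badly reported ones may be rejected more often, or rescued by revision when they would otherwise have failed. By making rejection and publication outcomes to compare by arm, the protocol accepts that the intervention may affect them.

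If it does, the two published groups are different selections from the two randomised groups, and their mean scores can differ although no article was improved. Defining the sample as published manuscripts makes the missing scores disappear by definition; it does not make the groups comparable. A journal deciding whether to adopt the reminder would want to know whether reports got better or weak reports were turned away, and the planned primary analysis alone cannot tell the two apart.

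**Working it through.** **Inputs from the protocol (Sample size).** Scenario 2: mean 0.71 in control and 0.82 with intervention, difference 0.11, SD 0.25, two-sided 5% t-test, 83 published articles per arm, 80% power.

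**Assumptions.** The protocol gives no publication rate and no correlation between reporting quality and publication. The main illustration takes 45% published in control and 40% with intervention.

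1. *The plan's own figure.* SE = 0.25 × √(2/83) = 0.0388. Power for 0.11 from the exact t-test is 80.5%, and the smallest sufficient size is 83 per arm. The stated figure reproduces. It counts published articles, so this point does not affect it.

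2. *Extreme case: all extra rejections are the worst reported, and no article is improved.* Share removed: q = 1 − 0.40/0.45 = 11.1%. Scores follow a beta-binomial on 10 items with mean 0.71 and SD 0.25. The lowest 11.1% are all scores of 0 to 3 items and a few of 4, with mean 0.220. Shift = q/(1 − q) × (0.71 − 0.220) = 0.125 × 0.490 = **+0.061**. Then 0.061/0.0388 = 1.57, and the t-test rejects about **35%** of the time with SD 0.25 kept in both arms. At 45% versus 43% the shift is 0.027 and the rejection rate 11%.

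3. *Opposite extreme: the best reported are lost.* The top 11.1% all score 10 of 10. Shift = 0.125 × (0.71 − 1.00) = **−0.036**.

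4. *Moderate selection, equal in both arms.* Publication and score follow a latent bivariate normal model with correlation ρ. Bias = 0.25 × ρ × [λ(0.40) − λ(0.45)], where λ(p) = φ(z)/p and z is the normal quantile cutting off an upper tail of p. With λ(0.40) = 0.966 and λ(0.45) = 0.880:

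| ρ | Bias | Rejection rate |
|---|---|---|
| 0.3 | 0.006 | 5.3% |
| 0.5 | 0.011 | 5.9% |
| 0.6 | 0.013 | 6.3% |

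 For drops of 5 to 10 points from publication rates of 30%, 50% or 70%, with ρ of 0.3 or 0.6, the bias is 0.006 to 0.036 and the rejection rate 5.2% to 15.4%.

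5. *Equal publication rates, stronger selection on reporting in the intervention arm.* Bias = 0.25 × (ρ₁ − ρ₀) × λ(p). For ρ of 0 versus 0.2, or 0.2 versus 0.5, and p of 0.3 to 0.7, the bias is 0.025 to 0.087 and the rejection rate 10% to 61%. A comparison of publication rates would show nothing.

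6. *Power of the planned rate comparison.* Randomised per arm: 83/0.45 ≈ 184. SE = √[(0.45 × 0.55 + 0.40 × 0.60)/184] = 0.0515. Power = Φ(0.05/0.0515 − 1.96) = Φ(−0.99) ≈ **16%**. At publication rates of 30%, 50% and 70%, power for a 5-point difference is 26%, 15% and 13%.

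7. *The wording on populations.* If all outcomes are calculated in published manuscripts and only time to first decision is extended, the proportion published is 100% in both arms. The same paragraph promises to test whether that proportion differs, so its sentences do not fit together.

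8. *What trimming bounds would show.* Suppose the observed difference is 0.11 with 45% versus 40% published, and control scores are as in step 2. Trimming the control arm by 11.1% from the bottom gives 0.11 − 0.061 = 0.049; from the top, 0.11 + 0.036 = 0.146.

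**The case against.** **Published articles are the deliberate target.** The Abstract states the hypothesis for published trials, and the Discussion explains the choice as pragmatic. For a journal, stricter filtering is one way the reminder could raise the standard of what it prints. This stands: the primary comparison should stay. But the intervention works by asking reviewers to request missing items, so a reader will take a positive result to mean improved reports.

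**The limitation is partly acknowledged.** The Discussion says that all versions of randomised manuscripts would ideally be analysed and cites confidentiality and resources as the obstacle; rejection and publication are compared by arm. This also stands in part. The Discussion does not name selection as a threat, and a rate comparison neither bounds the bias nor detects it at equal rates.

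**The no-missing-data sentence is true for the population as defined.** So it is. The fault is in using it to set aside losses after randomisation.

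**A sensitivity analysis may sit in an analysis plan not shown.** Its absence from this article is therefore not the point. The point is the reasoning that the article does state.

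**A reader might infer that the type I error is about 35%, or that a positive result would be mostly selection.** The documents support neither. The 35% requires deterministic rejection of the lowest scores at assumed publication rates. Milder selection at the same rates leaves the rejection rate near 5% to 6%, and the bias can run against the intervention.

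**A reader might also want a significant result accepted only if the bounds exclude zero.** That is too costly. In simulations with a true effect of 0.11 and no effect on publication, also requiring the confidence interval of the lower bound to exclude zero cut successful claims from 80% to about 44% in one and 52% in another, because of chance differences in publication rates.

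**Conclusion.** The point holds as a matter of interpretation and wording; it does not make the primary comparison or sample size wrong. The analysis conditions on an event after randomisation that the protocol itself treats as a possible effect of the intervention, and the stated reasoning sets the consequence aside.

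The size is uncertain. Assuming 45% versus 40% published, the bias runs from about 0.01 under moderate selection equal in both arms to +0.061 at the extreme, with −0.036 if the best reported are lost, against a planned 0.11. All of this rests on assumed publication rates and selection patterns. The planned rate comparison is weak protection even when read as covering all randomised manuscripts, and as literally worded it would be empty.

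**What to change.** Keep the primary comparison and the sample size, and make these changes:

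1. In Populations of analysis, replace the no-missing-data reasoning with a statement that the effect is conditional on publication and may combine improved reporting with selection of which manuscripts are published.
2. State that first-round rejection and publication are analysed in all randomised manuscripts.
3. Add Lee trimming bounds for the primary outcome as a sensitivity analysis. Trim the arm with the higher publication fraction by the excess, once from the bottom and once from the top of its scores, and report both bounds with confidence intervals. State the assumption behind them, that the intervention moves publication in one direction only; this could fail if some manuscripts are rejected and others rescued. State also that the bounds do not capture different selection at equal publication rates.
4. Use the bounds to qualify the interpretation, not as a condition for claiming success.

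The cost is a few lines of text and analysis. The bounds need only the published scores and each arm's randomised and published counts, which the trial already collects. The downside is a more cautious interpretation if publication rates differ.
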